### Sample size calculation

For both types of fractures (distal radius and ankle), the sample size was determined separately for both patient groups. Based upon a margin of non-inferiority, which is often the smallest value with a clinically important effect [29], of 9 points on the DASH and OMAS (which is based upon what is assumed to be clinically significant [30]) and a standard deviation of 14 [31] and 20 [32], respectively, 70 distal radius and 142 ankle fractures are necessary to demonstrate non-inferiority (power 0.85, alpha 0.05).

To enable a sensitivity analysis for evaluating the study outcomes for two relevant subgroups (that is, conservatively and surgically treated patients), more patients are needed. Based on the empirical treatment ratio for conservative:surgical of 8:2 for distal radius fractures and 5:5 for ankle fractures, we calculated that 142/0.5 = 284 patients with ankle fractures and 70/0.2 = 350 patients with distal radius fractures will need to be included. Accounting for a 10% loss to follow-up means 312 patients with an ankle fracture and 385 patients with a distal radius fracture are to be recruited.

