### Statistical analysis

Data will be analyzed using the IBM SPSS version 20 or higher (Armonk, NY: IBM Corp.). Characteristics of the patients in the treatment groups will be presented using descriptive statistics (mean ± standard deviation, median (range) or proportion) to assess if balanced groups were obtained after randomization.

The data analysis will be conducted according to the intention-to-treat principle, with a normal approximation for all questionnaires at 6, 12, 26 and 52 weeks for both types of fractures. For analysis of the primary study outcome, linear and generalized multilevel analyses will be used accounting for dependency within hospitals, clinicians and patients over time (four-level model). This means, among other things, that the data are to be analyzed longitudinally and, thus, the follow-up measurements are to be incorporated in the analyses. Results will be expressed as confidence intervals and these will be subsequently compared to the margin of non-inferiority in order to make inferences about the non-inferiority of the new intervention strategy. In addition to crude analyses, all analyses will also be adjusted for pre-defined prognostic factors, such as age, gender and fracture type. In a secondary analysis, a per-protocol analysis will be conducted which will account for ‘contamination’, meaning those randomized to the intervention group but nonetheless requiring follow-up imaging not allowed in the original treatment design (because there was a clinical indication for imaging).

The secondary clinical outcome measures of quality of life and pain will be analyzed in the same way as the primary outcome measure. The secondary outcome measures of ROM and complications will be compared between the ‘usual care’ group and the ‘reduced images’ group over time.

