The cost questionnaires will be used to perform an economic evaluation, which will be conducted from a societal perspective alongside the randomized controlled trial. The aim of the economic evaluation is to measure, value and analyze total costs of patients with distal radius and ankle fractures and to relate the difference in costs to the difference in effects between the intervention group which will receive only the initial follow-up radiographs (at 1 and 2 weeks) and the comparison (that is, usual care) which will receive imaging at the initial follow-up plus at 6 and 12 weeks. Both cost-effectiveness and cost-utility analysis will be performed. The time horizon of the economic evaluation is 12 months. Sensitivity analyses will be performed to assess the robustness of the results using different assumptions regarding costs and effects.

The underlying assumption surrounding missing data for this study is that the data are missing at random. Therefore, given the mixed model approach for the longitudinal analyses, missing data will not be imputed; however, we will correct for baseline covariates thought to be associated with the outcome, such as age, gender, and variables related to the condition (for example, fracture type), as well as variables thought to be related to missingness. In a sensitivity analysis, complete data sets will be compared to incomplete data sets in order to determine how robust these findings are.

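### The one missing-data check named in the article never varies the missing-at-random assumption, so it can call a non-inferiority result robust when poor outcomes in Group 2 are lost; the smaller subgroups are the exposed part

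*Protocol article*

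**What the plan says.** All of the missing-data text is in the Protocol article, Statistical analysis.

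- Assumption: "The underlying assumption surrounding missing data for this study is that the data are missing at random".
- Handling: "given the mixed model approach for the longitudinal analyses, missing data will not be imputed". The model is adjusted for baseline covariates linked to outcome, "as well as variables thought to be related to missingness".
- Robustness check: "In a sensitivity analysis, complete data sets will be compared to incomplete data sets in order to determine how robust these findings are".
- Decision rule: "Results will be expressed as confidence intervals and these will be subsequently compared to the margin of non-inferiority". The margin is 9 points on both scales (Sample size calculation).

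Two other sensitivity analyses are named, and neither concerns missing data. One belongs to the economic evaluation: "Sensitivity analyses will be performed to assess the robustness of the results using different assumptions regarding costs and effects". The other is the split by treatment: "To enable a sensitivity analysis for evaluating the study outcomes for two relevant subgroups". The per-protocol analysis deals with imaging contamination.

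The sample size allows for some attrition: "Accounting for a 10% loss to follow-up".

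**The concern.** A sensitivity analysis for missing data should change the assumption that the primary analysis cannot verify. Here that assumption is missing at random (MAR): given what was observed, the unseen scores resemble the seen ones. The stated comparison can be read in two ways.

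- *Completers against all available data.* Both estimates use observed scores only, and the completer analysis generally needs a stronger assumption than the mixed model.
- *Patients with complete data against patients with incomplete data.* This describes who was lost. It does not re-estimate the treatment effect.

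Neither reading asks what happens if the unseen scores are worse than the model predicts.

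The direction matters in a non-inferiority trial. Unseen poor outcomes in the reduced-imaging group pull the estimate towards non-inferiority. The outcomes are patient-completed questionnaires, no blinding is described, and patients know whether they had a radiograph. Leaving the study also means something different in each arm, because Group 2 leavers return to usual care. Loss related to outcome in one arm is therefore plausible enough to deserve a check that can detect its consequences.

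**Working it through.** **1. The plan's own figures.** Inputs from Sample size calculation: margin 9, SD 14 (DASH) and 20 (OMAS), power 0.85, alpha 0.05 with sidedness not stated. Assumed: true difference 0 and 1:1 allocation.

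n per arm = 2 × SD² × (z for alpha + z for power)² / 9²

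- One-sided 0.05: (1.645 + 1.036)² = 7.19. DASH: 392 × 7.19 / 81 = 34.8, so 35 per arm and 70 in total, as stated. OMAS: 800 × 7.19 / 81 = 71.0, so 142 in total as stated (144 if rounded up).
- One-sided 0.025: 88 and 178 in total, which do not match.

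The stated sizes thus fit one-sided 0.05, which corresponds to a 90% interval. The article does not state the interval level, so both levels are shown below.

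**2. Subgroup sizes.** From the same section: the wrist cohort of 350 splits 8:2, giving about 280 conservative and 70 surgical. The ankle cohort of 284 splits 5:5, giving about 142 each.

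**3. Tipping shift.** This is how much worse than MAR predicts the lost Group 2 patients must be, on average, before the confidence limit reaches 9 points, with Group 1 unchanged.

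- SE = 2 × SD / √N
- Half-width = 1.96 × SE (95%) or 1.645 × SE (90%)
- Tipping shift = (9 − half-width − observed difference) / fraction missing in Group 2

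Example, surgical wrist: SE = 28 / √70 = 3.35. The 95% half-width is 6.56, and (9 − 6.56) / 0.10 = 24.4.

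Results at 10% loss (observed difference counted against Group 2):

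| Population | N | Half-width 95% / 90% | Shift, observed 0: 95% / 90% | Shift, observed 2: 95% / 90% |
|---|---|---|---|---|
| Wrist, all | 350 | 2.93 / 2.46 | 61 / 65 | 41 / 45 |
| Ankle, all | 284 | 4.65 / 3.90 | 43 / 51 | 23 / 31 |
| Wrist, conservative | 280 | 3.28 / 2.75 | 57 / 62 | 37 / 42 |
| Wrist, surgical | 70 | 6.56 / 5.51 | 24 / 35 | 4 / 15 |
| Ankle, each subgroup | 142 | 6.58 / 5.52 | 24 / 35 | 4 / 15 |

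At 20% loss the shifts halve if N is held fixed: for the two smaller subgroup sizes, about 12 / 17 at observed difference 0 and 2 / 7 at observed difference 2. Fewer evaluable patients would lower them a little further.

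**4. Can the planned comparison detect the problem?** This was simulated under assumed conditions: four visits, correlation 0.6, SD 20, higher score worse, only the week-52 value missing, loss related to outcome in Group 2 only, true difference about 0, and 200,000 patients per arm. Negative values favour Group 2.

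| Mechanism | Loss | Bias of MAR model | Completer estimate | Gap, MAR estimate minus completers |
|---|---|---|---|---|
| MAR holds | 10% | 0.0 | −1.0 | 1.1 |
| MAR holds | 20% | 0.0 | −2.1 | 2.1 |
| Loss depends on week-52 score | 10% | −0.95 | −1.85 | 0.9 |
| Loss depends on week-52 score | 20% | −1.9 | −3.5 | 1.6 |
| Loss depends on the part of the week-52 score not predicted by earlier visits | 10% | −1.3 | −1.3 | 0.0 |
| Same | 20% | −2.5 | −2.5 | 0.0 |

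In the last mechanism the two estimates agree and both are biased. In the middle one they differ, but the completer estimate is the more favourable to Group 2, so it too would support non-inferiority. When MAR holds they also differ, although the mixed model is unbiased. Agreement therefore does not support MAR, and disagreement does not refute it.

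**The case against.** **It belongs in the analysis plan.** Detailed missing-data sensitivity analyses are commonly left there, and the plan and full protocol are not shown. A reader might infer that the trial has no analysis under informative loss. The article does not support that; it shows only that this is the one check named in it. The point stands because the article names a method and gives it the task of showing robustness. The text does not say that the comparison tests MAR, but robustness to missing data cannot be judged while that assumption stays fixed.

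**The check need not fail.** A reader might infer that it would always declare a biased result robust, or that the two estimates always agree. Neither follows: they differed in one of the two informative mechanisms simulated. The supportable word is *can*.

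**The bias is small.** At the planned 10% loss the simulated bias is about 1 to 1.3 points against a margin of 9. Overturning a whole-cohort result from an observed difference of 0 needs a shift of 43 points or more on a 100-point scale. This stands: a reader who concludes that the main verdicts are in danger goes too far. That safety depends on the observed difference, though. At 4 points against Group 2, the whole-ankle shift at 10% loss falls to 3.5 points (95%) or 11 (90%).

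**Not all subgroups are fragile.** Correct. The wrist figure of 70 is the surgical subgroup only; the conservative one, at about 280, is nearly as secure as the whole wrist cohort. The 4-point figure also needs a 95% interval; at the level that reproduces the sample size it is about 15.

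**There are safeguards.** The plan has reminders, attempts to trace drop-outs and adjustment for predictors of missingness, and Group 2 patients with symptoms can have radiographs without leaving. These make MAR more plausible and loss lower. They do not show what the remaining unseen scores would do to the conclusion.

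**Conclusion.** The point holds in a limited form. The only missing-data check named in the article does not vary the assumption on which the primary analysis rests, so its agreement with the main result would not be evidence of robustness to informative loss.

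The practical exposure is uneven. At 10% loss and no observed difference, both whole cohorts and the conservative wrist subgroup are fairly safe. The surgical wrist subgroup and both ankle subgroups are exposed, most clearly once the observed difference is about 2 points against Group 2 or loss reaches 20%.

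The sizes rest on assumptions that the article does not settle: the interval level, 1:1 allocation, equal SDs across subgroups, a simple two-group standard error in place of the four-level model, and loss that is informative in Group 2 only. The simulation adds an assumed correlation, assumed mechanisms and week 52 as the time point, which the article does not single out. The reasoning that the comparison leaves MAR untouched needs none of these. The change should be made, but it does not undermine the design.

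**What to change.** Keep the comparison of complete and incomplete data as description, state which reading is meant, and add a delta-adjusted tipping-point analysis:

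1. Impute missing DASH and OMAS scores under MAR, separately by arm, with the covariates already planned.
2. Leave Group 1 unchanged and worsen the imputed Group 2 scores in steps (higher DASH, lower OMAS).
3. Continue until the confidence limit crosses 9 points or the scale limit is reached. A short fixed grid, for example one ending at 15 points, would stop before most of the tipping shifts above.
4. Report the tipping shift for each whole cohort and each treatment subgroup, at the interval level used for the primary decision, with the fraction missing by arm beside it.

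The cost is a few sentences in the analysis plan, a few hours of programming and one more table. No data collection or sample size changes. The downside is that the robustness statement may be less reassuring, chiefly for the smaller subgroups.

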### Ethical considerations

The study design is in accordance with the Declaration of Helsinki, version Fortaleza (Brazil), October 2013 [33], and in accordance with the Dutch Medical Research Involving Human Subjects Act. Patients will not experience any benefit from participating in the study. No risk is involved for the group receiving usual care (Group 1). In Group 2 without standard radiographs after 2 weeks, the risk is considered minimal because radiographs will be made when clinically indicated.

This study is approved by the medical research ethics committee for all participating centers. The Medical Ethics Committee LUMC acts as central ethics committee for this trial (Number P14.086). An insurance which is in accordance with the legal requirements in the Netherlands (Article 7 WMO and the Measure regarding Compulsory Insurance for Clinical Research in Humans of 23 June 2003) has been obtained. This insurance provides cover for damage to research subjects through injury or death caused by the study. Once a year, information will be provided to the medical research ethics committee on the numbers of subjects included and numbers of subjects that have completed the trial, serious adverse events/serious adverse reactions, and other problems.

## Discussion

The current distal radius and ankle fracture protocols recommend radiographic assessment at all routine visits. It is questionable whether routine imaging following the initial follow-up (that is, after 2 weeks), after which definitive treatment is established (being surgical or conservative), is justified [8]. Three retrospective studies have suggested that radiographs performed beyond the 2-week follow-up result in longer waiting room visits, unnecessary radiation exposure and increased healthcare costs without providing additional clinical information which impacts clinical decision-making [8-10]. Alongside the clinical question about the justification of the radiographs after the initial follow-up period, a cost-effectiveness analysis is indicated as the current protocols appear not to be cost effective. A randomized controlled trial is needed to investigate whether a reduced imaging protocol can be conducted for less cost, but with no worse outcome than the current standard of care in those with distal radius and ankle fractures. This study will provide necessary data on (cost) effectiveness of routine radiography in the follow-up of distal radius and ankle fractures and could pave the way for a change in (inter)national protocols.

## Trial status

The trial started in July 2014, and is currently enrolling participants.

## Abbreviations

AAOS: American Academy of Orthopaedic Surgeons
DASH: Disabilities of the Arm, Shoulder and Hand Score
EQ5D: EuroQol-5D
LUMC: Leiden University Medical Center
OMAS: Olerud and Molander Ankle Score
PRWHE: Patient-Rated Wrist and Hand Evaluation
ROM: Range of motion
SF-36: Short Form-36
UMCG: University Medical Center Groningen
VAS: Visual analogue scale
Vumc: VU University Medical Center
WARRIOR: Wrist and Ankle fractures Routine RadIOgraphy Reduction
